### Research hypothesis

We hypothesize that RT will be more effective than standard care in improving clinical health status. The main hypothesis is that by applying a supervised RT (EXER-COVID Crossover Study) for 6 weeks, we could reduce the perception of persistent symptoms. We could increase physical performance (V̇O_2_max and/or muscle fitness) through the effects of mechanical and endocrine action, and we could modulate the production of immunological and inflammatory markers due to skeletal muscle contraction, which could contribute to reducing the inflammatory process that is usually established in COVID-19 infection. Exercise training is also expected to be more effective in improving cardiovascular measures of resting blood pressure, arterial stiffness, and heart rate variability as compared to no training. If successful, our trial would provide evidence that exercise training has potential for patients with postdischarge symptoms after COVID-19.

## Methods

### Study design

The trial will be a monocentric, randomized, crossover design registered with the Clinical Trials Registry (NCT04797871 [First Posted: March 15, 2021, Last Update Posted: May 17, 2022]). All items from the ClinicalTrials.gov registry platform can be found within the protocol. This is a superiority trial, with equal allocation to intervention and control groups. The protocol will be developed according to the Standard Protocol Items: Recommendations for Interventional Trials (SPIRIT) guidelines (see Additional file 1) for randomized controlled trials (RCTs) [39].

### Participant eligibility

A total of 100 adults of both sexes between 20 and 60 years old will be recruited from the Hospital Universitario de Navarra (HUN). At the HUN site, participants will be admitted from internal medicine service referrals and from participant databanks of patients who have consented to be contacted for participation in research projects. All patients will be screened for inclusion by a physician to ensure that the patient has been diagnosed with COVID-19 and has no other psychiatric or somatic condition that can explain the persistent COVID-19 symptoms. Potential participants will fulfill the following inclusion criteria: over 18 years of age, diagnosed with SARS-CoV-2 using real-time reverse transcriptase polymerase chain reaction (PCR) tests or testing positive for SARS-CoV-2 virus antigen >90 days before randomization, presenting with a chronic symptomatic phase lasting >90 days since the onset of symptoms, has not been hospitalized, has no evidence on clinical records of pneumonia or any other organ failure related to SARS-CoV-2, and is capable and willing to provide informed consent. Patients previously treated for persistent COVID-19 symptoms (i.e., physical therapy or rehabilitation); patients who are pregnant or breast-feeding; patients with cardiovascular or endocrine comorbidities (i.e., atrial fibrillation, acute myocarditis, acute heart attack or unstable angina, aortic stenosis, acute endocarditis/pericarditis, uncontrolled high blood pressure, acute thromboembolism, severe heart failure, respiratory failure, and uncontrolled acute decompensated diabetes mellitus or low blood sugar) or other neurological or musculoskeletal comorbidities that will prevent safe exercise participation; patients with pain that is made worse with exercise; patients with cognitive, communication, or behavioral issues that may limit their safe participation in the exercise program, or contraindications that will prevent their participation in the exercise intervention; and patients who have been treated with IL-6 receptor antagonists (tocilizumab, kevzara) within the last month, due to drug interference with the cardiopulmonary exercise adaptations, will be excluded.

### Randomization, allocation concealment, and blinding

Eligible participants will be randomly assigned to one of 2 sequence orders with a 1:1 allocation using a computer-generated block randomization schedule (Research Randomizer V.4). Assignment will take place through previously constructed balanced blocks, which will allow equiprobable assignment and ensure that each group has the same number of participants. This allocation mechanism will be carried out until 100 total participants are assigned. The assignment keys will be kept in a confidential file in the Navarrabiomed center and will be opened at the end of the study’s analyses. To ensure masking, an alpha-numerical code will be assigned to each study group. This code will be delivered to the associated researcher and will not be revealed to the investigators in charge of processing the data until the analysis of the coded interventions is completed. Additionally, the researchers from the Navarrabiomed center will be responsible for preparing reports for the participants’ safety committee to verify the progress of the study. Following the conclusion of the baseline examination, the appropriate envelope will be opened by a study researcher, and the participants will be informed about their group allocation. Assessors of outcomes will be blinded to patient data, including allocation at baseline and follow-up. Blinding will be used for all laboratory analyses. Owing to the nature of the study, patients cannot be blinded to the exercise training modality.

### Procedure for unblinding if needed

Not applicable. This study is an unblinded, practice-level intervention.

### Procedure

Participants will be randomly assigned (1:1) to one of 2 sequence orders using computer-generated random numbers. All participants will complete both group interventions. Therefore, as participants will act as their own control, this approach will remove any potential differences between subjects and reduce the potential bias when estimating the intervention effect. First, eligible and consenting participants will start with the baseline assessment (T0). Second, participants will be assigned to start 6 weeks of either control group (Sequence 1) or exercise training (Sequence 2), T1 (week 6). Third, full crossover occurred after the 6 weeks, during which participants completed a second 6-week period of the opposite condition (T2, week 12). Outcome assessments will be performed at the end of the immediate intervention and control phase and at the end of the crossover intervention phase (Fig. 1). The general procedure is shown in Fig. 2.

**Fig. 1 Fig1:**
[figure not shown]
Schedule illustrating enrolment and interventions (SPIRIT figure) of the “EXER-COVID Crossover Study”. T: time-point; *According to SPIRIT 2013 statement. ** A random subsample of participants (20 subjects in each group, *n*=40)

**Fig. 2 Fig2:**
[figure not shown]
Flow of subjects through the “EXER-COVID Crossover Study”. Participants will be first randomly assigned to a 6-week period of no-exercise training (Sequence 1, *n*=50) or exercise training (Sequence 2, *n*=50) after which full crossover occurred. T: time-point; PROMs: patient-reported outcome measures; REE: resting energy expenditure; HRV: heart rate variability; BP: blood pressure

### Intervention

All interventions will take place at the Biomedical Research Center of Navarra (Navarrabiomed) site facilities. Standard medical care will be provided to all participants in all groups. The exercise intervention will consist of 6 weeks of individualized supervised muscle power RT, two sessions per week performed on nonconsecutive days to avoid overtraining and maximize adaptations. To reduce the risk of COVID-19 reinfection, a 1:1 trainer-to-participant format will be used during training sessions. On the training days, the participants will warm up with 3 sets of 10 repetitions of half air squats with the participants’ own body weight followed by 10 min on an electronically braked cycle ergometer (Lode Excalibur Sport, Groningen, The Netherlands) at 50% of the VO_2_peak and 4 sets of 30 s followed by 90 s of passive recovery at 100–120% of the VO_2_peak. EGYM Smart Strength machines (eGym® GmbH, München, Germany) will be used for both RT and maximum strength and muscle power measurements of the lower and upper extremity muscles. Muscle power RT, including motivational gamification and maximum acceleration of constant weight from 50 to 70% of daily maximum strength measurements, will be used during training (Explonic eGym® intelligent training program).

The RT intervention will comprise 3 sets of 8 to 12 repetitions with a load equivalent to 50 to 70% of the daily 1-repetition maximum (1 RM) for all major muscle groups (i.e., the exercises for the upper body include pectoral press and back press, and the exercises for the lower body include leg press and leg extensions). All movements will be performed at 100% of the maximum speed achieved during the propulsive phase (i.e., as fast as possible according to the patient’s muscular and functional capacity). The recovery between sets will be between 1 and 2 min. At the end of the session, there will be 5 min of stretching to cool down. The duration of the sessions will be 30–45 min, and the duration of the entire program will be 6 weeks, equivalent to 12 sessions. See Table 1 for details.

**Table 1 Tab1:** Supervised exercise program for “EXER-COVID Crossover Study”

Weeks	1		2		3		4		5		6	
***Session***	***1***	***2***	***3***	***4***	***5***	***6***	***7***	***8***	***9***	***10***	***11***	***12***
Warm up	3 sets of 10 reps of bodyweight half squat+ 10 min at cycling at 50% of V̇O_2_peak+4 sets of 30 s at 100–120% of V̇O_2_peak											
Strength training												
Exercises	Pectoral press, back press, squat press and knee extension											
Warm up	2 sets of 5 reps at 30–40% of daily maximum strength											
Sets	3	3	3	3	3	3	3	3	3	3	3	3
Repetitions	10	10	12	12	10	10	12	12	8	8	10	10
Intensity (1 RM %)	50	50	50	50	60	60	60	60	70	70	70	70
Cool down												
Stretching	5 min of static and dynamic flexibility exercises											

*1 RM* one-repetition maximum

The no-exercise (control group) will receive standard hospital care, which includes rehabilitation when necessary. Standard care will rigorously conform with all the standard care steps in the current COVID-19 management protocol, and participation will not affect the patients’ treatment or the care they receive during recovery from the disease during the study or in the future. As described at the beginning of the procedure section, this protocol will use a crossover design in which the intervention group will receive the intervention (RT) during the first phase (6 weeks) followed by standard medical care during the second phase (6 weeks). The control group will receive the treatments in the reverse order (standard treatment first followed by the RT intervention). This will allow us to make individualized adjustments, allowing each subject to serve as their own control. If participants desire to stop training and develop health conditions (i.e., SARS-CoV-2 reinfection) or injury that precludes safe participation of exercise over the course of the intervention, we will discontinue training. Participants will be asked to not participate in another structured exercise regimen or intervention over the course of their participation in either the intervention or control group; otherwise, they will not be allowed to continue participation.

### Outcome measures

The measurements include a medical health interview and examination (e.g., body measures, blood pressure, heart rate, ECG), a V̇O_2_max test, a whole-body dual-energy X-ray absorptiometry (DXA) scan, blood samples, 1-repetition max for upper and lower body muscles, and questionnaires (PROMs: patient-reported outcome measures, physical activity levels, diet recall, quality of life, etc.). The questionnaires will be administered online using SurveyMonkey. Participants will receive an email with a personal link to fill out the questionnaires. For optimal retention, participants will be contacted by the research assistant if they have not completed the questionnaires within 1 week. Outcome measures will be assessed at T0, T1, and T2. See Fig. 2 for the measurements at all time points.

### Primary outcome

The primary outcome is the change in aerobic exercise capacity measured by (V̇O_2_max) before and after the intervention period. Graded exercise tests will be performed on a bicycle ergometer (Lode B.V., Groningen, The Netherlands) to determine the maximal oxygen uptake. The test will start with a 3-min warm-up at 25 W. Warm-up will be immediately followed by a 25-W increase every 2 min until exhaustion, which is categorized as voluntary exhaustion or failure to maintain rounds per minute above 60. Breath-by-breath gas exchange data will be collected using a metabolic gas analyzer (QUARK, Cosmed, Rome, Italy) and used to determine V̇O_2_max and total energy expenditure during exercise. The staggered phase will have a maximum duration of 8 to 12 min, and the cadence of the pedal will not be altered during the effort (approx. 1.23 Hz or 50–60 RPM). The heart rate (HR) will be measured with a cardiotachometer (Polar Vantage NV, Finland) every 5 s.

### Secondary outcomes

#### Long-term COVID manifestations

Data on specific symptoms potentially correlated with long-term COVID-19 will be obtained using a standardized questionnaire administered at enrollment via PROMs [40]. At baseline and at the end of each crossover period, participants will be asked about the presence or absence of symptoms related to long-term COVID-19 and whether each symptom persisted at the time of the visit. More than 1 symptom could be reported that reflects symptoms such as functional limitations and clinical characteristics (i.e., nausea/vomiting, impaired visual acuity or blurry vision, anosmia, dizziness, depression, chills, weakness, musculoskeletal pain, palpitations/tachycardia, change of appetite, frustration, cognitive involvement, anxiety/irritability, dryness, impaired concentration, and headache).

#### Inflammatory markers

Inflammatory markers will be assessed following an overnight fast (10–12 h). Blood samples (2.7 ml EDTA plasma, 7.5 ml serum, 4.9 ml lithium-heparin, 5 ml citrate plasma) will be collected and processed by a trained laboratory nurse and analyzed according to standard procedures. Plasma will be stored at −80 °C prior to analysis. Blood samples will be analyzed for preliminary medical examination (i.e., full blood count, albumin, creatinine, urea, potassium, sodium, calcium, CRP, GGT, ALT, D-dimer, creatine kinase, TSH, T3, and T4). At the two experimental study visits (T0–T1 and T2), blood (2 × 7.5 ml serum) will be collected for a cytokine human immune monitoring panel using a commercial array (ProcartaPlex™, MAGPIX 65-Plex, Ref: EPX650-10065-901), including *cytokines* G-CSF (CSF-3), GM-CSF, IFN alpha, IFN gamma, IL-1 alpha, IL-1 beta, IL-2, IL-3, IL-4, IL-5, IL-6, IL-7, IL-8 (CXCL8), IL-9, IL-10, IL-12p70, IL-13, IL-15, IL-16, IL-17A (CTLA-8), IL-18, IL-20, IL-21, IL-22, IL-23, IL-27, IL-31, LIF, M-CSF, MIF, TNF alpha, TNF beta, and TSLP; *chemokines* BLC (CXCL13), ENA-78 (CXCL5), Eotaxin (CCL11), Eotaxin-2 (CCL24), Eotaxin-3 (CCL26), Fractalkine (CX3CL1), Gro-alpha (CXCL1), IP-10 (CXCL10), I-TAC (CXCL11), MCP-1 (CCL2), MCP-2 (CCL8), MCP-3 (CCL7), MDC (CCL22), MIG (CXCL9), MIP-1 alpha (CCL3), MIP-1 beta (CCL4), MIP-3 alpha (CCL20), and SDF-1 alpha (CXCL12); *growth factors/regulators* FGF-2, HGF, MMP-1, NGF beta, SCF, and VEGF-A; and *soluble receptors* APRIL, BAFF, CD30, CD40 L (CD154), IL-2R (CD25), TNF-RII, TRAIL (CD253), and TWEAK. Molecules showing significant differences between the two patient cohorts in marker levels and changes will be validated by ELISA. Blood samples will be stored at − 80 °C for future potential analyses, such as metabolomics, exosome isolation, and/or molecular analyses.

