### Isolating the peripheral blood mononuclear cells (PBMCs) and metabolomic analysis

A random subsample of participants (20 subjects in each group, *n*=40) will be included to isolate the PBMCs by Ficoll gradient, as previously described [41]. The following fluorochrome-conjugated antibodies will be used: CD4, CD8, PD1, CD62L, KLRG1, CD28, CD57, CD163, CD119, CD56, CD116, CD66b, CD11b, and CD14. Cells will be washed, stained and analyzed by flow cytometry. In addition, plasma lipid extraction will be performed and then analyzed by ultrahigh-resolution liquid chromatography coupled to mass spectrometry (UHPLC–MS) using ultrahigh-resolution liquid chromatography coupled to mass spectrometry (UHPLC–MS) using the technique described by Barr et al. [42]. In summary, plasma lipid extraction is a liquid extraction of the serum with chloroform/methanol (2:1) and a saline solution of sodium chloride followed by incubation the mixture for 1 h at −20 °C to promote the precipitation of proteins. Next, the sample is evaporated in an evaporating concentrator, and the dry extract is reconstituted in acetonitrile/isopropanol. After centrifugation, the supernatant is analyzed by UHPLC–MS. For this purpose, the chromatographic column UPLC BEH C18, 2. 1×100 mm, 1.7 μm (Waters Corp. Milford, MA, USA) will be used, with a mobile phase consisting of a binary mixture formed by H_2_O/acetonitrile/10 mM ammonium formate and acetonitrile/isopropanol/10 mM ammonium formate. The conditions of chromatographic separation and high-resolution mass spectrometry (Xevo G2 QToF, Waters Corp.) have been previously described [43].

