### Statistical procedures

#### Sample size

Given the absence of exercise interventions for patients with persistent COVID-19 symptoms [57], in this area, a conservative approach will be used to estimate the sample size. Inspired by a Lau et al. study [58], it is expected that the exercise group will increase cardiorespiratory fitness at least 1-MET (3.5 mL/kg/min) more than the standard care group with an SD of 5.4%. A sample size of 84 participants (42 per group) provides statistical power (1−*β*) of 80% using a two-tailed alpha <0.05 and adjustment for baseline value and other prognostic covariates [59]. This sample size will also be sufficient for detecting differences in our secondary biomarkers and patient-reported outcomes. Considering a potential dropout rate of <15–20% based on our previous exercise trials [60, 61], a total of 100 participants (50 per group) will be randomized. This power will also be sufficient for detecting differences in our secondary biomarkers and patient-reported outcomes if the effects are moderate (i.e., effect size of Cohen’s *d* ≥ 0.6). This power is not sufficient for detecting potentially meaningful differences in any of the exploratory clinical outcomes. Given that the purpose of this phase II trial is to inform larger phase II and III trials, the patient-reported and clinical outcomes will also be interpreted for potential clinical significance based on the direction and magnitude of numerical differences. These calculations were performed with the Power and Sample Size Calculations program, Version 2.1.23.

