#### Methods in analysis to handle protocol non-adherence and any statistical methods to handle missing data

The study follows an intention-to-treat principle with the use of baseline observation carried forward imputation, where the baseline value will replace missing data [61]. The final analysis population will be fully described and differences from the enrolled population will be presented. Cases that are lost may remain in the analysis, although they will provide less information and reduce the variance of estimated effects less than cases that are present for all measurement times. Adherence will be the number of group sessions attended/in sessions completed by each participant divided by the total number of sessions available × 100. Retention will be the number of participants who remained in the training program for all 6 weeks divided by the total number of participants × 100. Satisfactory adherence is defined as a minimum of ≥80% adherence to the prescribed RT sessions. Any discrepancies in data analysis between the methods will be resolved by a third-party biostatistician. First, descriptive statistics for the overall sample and between groups will be calculated. Second, a sequence 1–2 crossover analysis will be conducted using *t* tests and/or ANOVA to determine changes in primary and secondary continuous outcomes with individual participants as blocking factors. Categorical outcome measures will be analyzed using a McNemar test for data combined across both periods of the crossover. In addition, the proportions of participants reporting or not reporting long-term COVID-19 symptoms at the end of each period will be compared using a 2-proportion *z* test. If this test yields a statistically significant result, the usual test for differences between the effects of the two treatments should not be applied. By neglecting carryover effects using the procedure of Gaus and Högel [62], we expect enough power for investigation of differences. All analyses will be 2-sided. An *α* value ≤.05 will be considered to indicate statistical significance for the primary analysis.

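### The rule for picking molecules from the 65-analyte panel compares sequences rather than treatments, states no error control, and calls same-trial ELISA validation; the power sentences also cover a 20-per-group subset

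*Protocol article*

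**What the plan says.** The protocol article makes four statements that bear on this point.

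- **Selection rule (Inflammatory markers).** A commercial 65-plex panel is measured at the study visits, and then "Molecules showing significant differences between the two patient cohorts in marker levels and changes will be validated by ELISA". The section does not define the cohorts, the visit or the threshold.
- **Analysis (Methods in analysis to handle protocol non-adherence and any statistical methods to handle missing data).** Continuous primary and secondary outcomes get a crossover analysis by t tests or ANOVA, with participants as blocks. "All analyses will be 2-sided", and the only threshold given is that a "value ≤.05 will be considered to indicate statistical significance for the primary analysis".
- **Power (Sample size).** "A sample size of 84 participants (42 per group) provides statistical power" of 80%, with adjustment for baseline and other covariates. Secondary biomarkers are then covered twice, first without condition: "This sample size will also be sufficient for detecting differences in our secondary biomarkers and patient-reported outcomes". The second time there is a condition, Cohen's d of at least 0.6: "This power will also be sufficient for detecting differences in our secondary biomarkers and patient-reported outcomes if the effects are moderate".
- **Subset (Isolating the peripheral blood mononuclear cells and metabolomic analysis).** Cell phenotyping is done in "A random subsample of participants (20 subjects in each group", 40 in all. The Objectives section names lymphocyte immunophenotypes as a measure for the secondary objective.

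**The concern.** The immunological and inflammatory profile is part of the main hypothesis in the Abstract, so how molecules are chosen and described matters.

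- Read literally, the rule compares groups of people who all receive both conditions. That is not the effect the trial is designed to estimate.
- A screen of 65 analytes by plain significance is expected to yield some chance findings.
- A second assay on the same blood carries the same sampling error, so a chance difference can be confirmed and reported as validated.
- The power sentences make no exception for markers measured in fewer than half of the participants.

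**Working it through.** **1. The plan's own power figure.** Inputs from Sample size: 42 per group, two-sided 0.05, d = 0.6, stated power 80%.
- Normal approximation: Φ(0.6 × √(42/2) − 1.96) = Φ(2.75 − 1.96) = 78.5%. The noncentral t gives 77.6%.
- With baseline adjustment, which the section assumes, the SD shrinks by √(1 − r²). At an assumed r = 0.3 the power is about 81%.
- In the planned crossover, dz = 0.6/√(2(1 − r)). With N = 84 and r = 0, dz = 0.424 and power is 97%; it is higher for any positive r.

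For one marker in the full sample, the stated power is therefore essentially reproduced.

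**2. What a between-cohort comparison estimates.** From Procedure, Sequence 1 is control then exercise, and Sequence 2 is exercise then control.
- T0: nobody has been treated, so any difference is chance under randomisation.
- T1: Sequence 2 has trained and Sequence 1 has not. This is exercise versus control.
- T2: both have trained, Sequence 1 recently and Sequence 2 earlier. This is not exercise versus control.
- Change from T0 to T2: both sequences have had both conditions, so this is not the contrast either.

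Only the T1 level and the T0-to-T1 change give the intended contrast directly. The rule does not restrict itself to these, and the within-participant analysis does not compare cohorts.

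**3. Chance findings.** The analytes listed are 33 cytokines + 18 chemokines + 6 growth factors or regulators + 8 soluble receptors = 65. Alpha of 0.05 for the panel is an assumption.
- Expected false positives if all are null: 65 × 0.05 = 3.25. If levels and changes are both tested: 130 × 0.05 = 6.5. Correlation between analytes does not alter these expectations.
- Chance of at least one in 65 tests: 1 − 0.95^65 = 96% if independent. By simulation with equal correlation 0.3, 0.5 and 0.8 between test statistics, it is about 87%, 68% and 32%.
- If 10 of the 65 truly differ at d = 0.6 (illustration, 42 per group): 55 × 0.05 = 2.75 false and 10 × 0.776 = 7.76 true, so 2.75/10.51 = 26% of the selected molecules are false.

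**4. What ELISA adds.** Take a null marker already selected, and re-measure it in the same samples. If the two assays' test statistics correlate 0.7, 0.9 or 0.95 (assumed), it is significant again in the same direction in about 33%, 59% or 71% of cases (simulation). In independent participants that chance would be about 2.5%.

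**5. The immunophenotype subset.** 20 per group, d = 0.6, two-sided 0.05.
- Per-group comparison: Φ(0.6 × √(20/2) − 1.96) = 47.5%; the noncentral t gives 46%. Power of 80% needs d of about 0.91.
- Crossover analysis of all 40, with 38 degrees of freedom: r = 0, dz = 0.424, 74%; r = 0.3, dz = 0.507, 88%; r = 0.5, dz = 0.600, 96%. The correlations are assumed, and so is the absence of carryover.

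**The case against.** A journal article condenses the full protocol, and multiplicity rules for a 65-plex panel usually sit in an analysis plan, which is not shown. The article ties 0.05 to the primary analysis only. This stands: the lack of an adjustment rule is not in itself the finding, and 0.05 for the panel is an assumption. But the article does fix a selection rule, and an unseen adjustment would change neither its between-cohort wording nor what ELISA on the same blood can show.

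The cohorts might loosely mean the exercise and control conditions. If so, the conflict is one of wording, but the text still has to say it.

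Following a multiplex screen with ELISA is ordinary practice in a trial that calls itself phase II, and the section does not claim that ELISA proves a group difference. That is fair. It supports labelling the panel exploratory, which the text does not do. That the ELISA uses the same participants' blood is inferred; no other source is described.

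On the subset, Methods for additional analyses says the PBMC and metabolomic work follows the primary plan, so the crossover figures are closer to the intention than 46%. They rest on an assumed correlation and no carryover, and at r = 0 power still falls below 80%.

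A reader might go further and infer that the stated power fails for secondary biomarkers in general. The documents do not support this. The unadjusted shortfall is 2.4 points (77.6% against 80%), and it disappears with modest baseline adjustment or in the planned crossover. Nor do they support the inference that adjusting for 65 tests leaves almost no power per marker. That requires a Bonferroni correction combined with a parallel comparison, and the article specifies neither for the panel. Even under Bonferroni, the crossover with N = 84 gives 65% to 97% at d = 0.6 for r from 0 to 0.5.

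**Conclusion.** The point holds for the selection rule, for the word used for the ELISA step, and for the scope of the power sentences. It does not hold as a general failure of power for single full-sample markers.

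- The rule is not an exercise-versus-control contrast after T1, and it conflicts with the crossover analysis. This needs no numerical assumption.
- At an assumed 0.05, 3.25 chance hits are expected if no analyte responds, or 6.5 with levels and changes. The chance of at least one is 96% under independence and lower under correlation.
- Same-blood ELISA checks the assay. It cannot reliably remove chance differences.
- The power sentences are too broad. The first has no effect-size condition, and neither separates out the subset, where power at d = 0.6 is 46% per group or 74% to 96% in a crossover.

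The primary V̇O₂max result is not affected.

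**What to change.** 1. In Inflammatory markers, replace the between-cohort wording with the treatment effect, tested once per analyte on the log scale with the same treatment contrast as the main analysis. A first-period comparison (T1 adjusted for T0) would also contrast exercise with control, but it discards the second period and its information. If chosen, that cost should be stated.
2. Select analytes for ELISA and for reporting by Benjamini-Hochberg at a 5% false discovery rate across the 65.
3. Call the ELISA step analytical confirmation, and label the panel exploratory.
4. In Sample size, limit both power sentences to single outcomes at d ≥ 0.6 measured in the full sample. State power for the immunophenotype subset separately: 46% at d = 0.6 and 80% at d of about 0.91 on the per-group basis, or 74%, 88% and 96% in a crossover analysis of 40 at assumed correlations of 0, 0.3 and 0.5 with no carryover.

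The cost is revised wording and a small amount of computation, with no new data. The downside is that fewer analytes will be declared significant.
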